### Clinics

Secondary prevention of nutritional intervention is implemented in nutrition clinics for subjects with diseases such as diabetes, overweight and obesity, dyslipidemia and hypertension. The expert dietitian fills out 24-hour dietary recall, food habits, and activity forms and gives away a diet manual according to each individual's situation. The dietitian also instructs the individual's diet along with nutrition education about exchange list and how to select foods, manage their diet and self monitoring skills. The follow up of individuals are done in proper intervals according to protocols. The protocols and cut off values are derived according to last medical nutrition therapy manual texts -therapeutic lifestyle changes (TLC) [42], DASH (Dietary Approach to Stop Hypertension) [43,44], restricted-energy diets [45] and 2007 ADA Nutrition Principles and Recommendations for persons with Diabetes Mellitus [46]. DASH and ADA nutrition principles and recommendations for diabetes, have been adopted for Tehranians in previous study [44] and from declarations of appropriate societies in Iran.

A quit smoking clinic has been established to help and support addicted people to quit smoking. In these clinics, general practitioners help the patients give up smoking by giving them face to face consultations, pamphlets and brochures.

### Schools

The School-based lifestyle modification subprogram is designed as a multidisciplinary health promotion program using a population approach that is underpinned by the Health Promoting Schools philosophy. All strategies are focused on adolescents aged 12 to 18 years. The program targets the whole school community including parents, students, staff, teachers and the school environment. It is intended to influence anti-tobacco practice and not simply knowledge in the schoolchildren. We selected those schools that had more distance from another area, in both control and intervention areas. The interference of students attended in schools in intervention and control areas is less than 8%

Twelve schools, 7 guidance and 5 high schools, across the intervention area and 15 schools (7 guidance and 8 high schools) across the control area are enrolled in the program. The living tobacco-free intervention program in schools consisted of four components: classroom curriculum and practice, students activities in school anti-tobacco society, anti-tobacco policies in school and family (parents) involvement. The intervention approach combines constructs from social learning theory and principles of Iranian culture and practices. At beginning of first year of program implementation in schools, all the principals and volunteer teachers are trained by physicians and dietitian in 2-day teaching seminars in order to enable team to educate schoolchildren in matters related to lifestyle modification. Related teaching programs in schools contain 4 main and 3 review lessons. Topics in these lessons are prevalence of smoking and its short term and long term consequences, psychology of coping with stress and methods of quieting smoking. Nutrition educational program includes three 30-minute nutrition classes per semester. The staff members who deliver the interventions are different from those who collect the data. The parental component of the intervention include two 45-minute nutrition classes in academic year and one class per year for teachers whom educate schoolchildren with the aim of promotion of food habits. The content of the nutrition lessons parallels the information offered in children's curriculum with the objective of introducing food groups based on food guide pyramid and nutrition concepts such as trying low-fat foods and dairies, high fiber diets, and healthy snacks. Food bulletin and pamphlets covers dietary issues for parents. The baseline survey showed that high fat, high sugar and salty snacks were sold in schools. After explaining to school officials, and schoolchildren, red labels are used for unhealthy snacks and green labels for healthy foods. Participation of parents are suggested by cooking healthy traditional foods and sold with low price to children. In each phase, KAP study of dietary issues is performed to help for further educational program.

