### Biostatistical considerations

#### Sample size

For baseline data collection, based on predicted prevalence rates of 30% for dyslipidemia in people <30 and 45% for those ≥ 30 years of age, confidence interval of 95%, study power of 80%, attrition rate of 20%, design effect of 2% for seven age groups and two sexes, sample size was calculated to be 14280. Therefore, 15005 subjects were selected randomly from areas covered by 3 health centers. In phase 2 of TLGS, based on 5% decrease in serum cholesterol, two gender, three age groups, 5% design effect and 30% attrition rate, sample size for intervention group was calculated as 4750 subjects. Therefore, population covered by one of the 3 health centers (5630 people) selected for intervention and 9375 subjects under coverage of other two centers used as controls.

Because of the wide scope of the project and variety of the measured variables, different types of analyses are performed, depending on the type of the reports or the variables and outcomes.

Although the original of this study was based on reducing hypercholesterolemia, however, in all subjects including those less healthy or normals, changes in other risk factors, NCD, and outcomes delineated in this study will also be followed in statistical considerations.

In most of analyses we will considered each individual separately, however, for interfamilial relations we will consider intraclass correlations in analyses. It should be also mentioned that in multistage cluster random sampling procedure, each health center in district 13 was a cluster and families in three randomly selected centers were recruited. Continuous data are expressed as their measures of location and spread in total and subgroups. For qualitative and categorized continuous variables, percentages and frequency distributions are reported.

Normality of distribution of the continuous variables will be examined using histograms, measures of skewness and kurtosis, Kolmogrove-Smirnove test and sometimes Chi-square test. When log-transformed values are used, geometric means are computed. Percentiles will be used to describe the high or low values of the skewed variables. When assumptions of the parametric statistical methods are not met, nonparametric methods of their counterparts will be used. These methods also were used for analysis of variables, not originally continuous, such as attitudes, quality of life etc.

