Incidence rates of NCDs such as diabetes mellitus, angina pectoris, myocardial infarction, hypertension etc., will be estimated adjusted mainly for age and sex. Relative risks for different factors and their 95% confidence interval will be reported.

Continuous variables will be compared between intervention and control groups using student's t-test. Analysis of variance (ANOVA) will be used to compare the variables among three or more subgroups followed by appropriate post hoc test such as Tukey. To adjust the comparison by the potential confounding variables, two or three-way ANOVA will be used. In addition, analysis of covariance will be employed when adjusting for a covariate correlated with the dependent variable. To compare the proportions between two or more groups, Chi-square test of independence and Fisher exact test will be employed. Matel-Haenszel test will be used when adjustment required. To compare the data with their baseline, paired t-test and repeated measures analysis of variance or McNemar, Sign and Friedman tests will be used.

To evaluate the relationship between variables, Pearson or Spearman correlation coefficients is used Multiple regression analysis will be used to find out the relationship between variables such as blood pressure, fasting blood sugar, lipid profiles and variables regarded as independent variables such as body mass index, waist circumference, lipid profiles, age, etc.

When the outcome variable was defined as dichotomous, for instance, diabetes mellitus, hypertension, etc., multiple logistic regressions was employed to assess the relation of potential risk factors and the outcomes. Multinomial logistic regression will be used when the outcome is defined as polychromous variable, e.g., diabetes mellitus, impaired glucose tolerance (IGT) and normal. Odds ratio and its confidence interval will be reported and interpreted. Secondary outcomes (e.g., mortality, cardiovascular morbidity) will be analyzed using life table method to evaluate the association of different factors on survival time, Cox regression analysis was performed. A proportional hazards regression model will be used to evaluate potential covariability that may modify the primary and secondary outcomes. The adequacy of the models will be checked, usually, using the Hosmer-Lemeshaw statistic. In addition, ROC curve and its area under curve (AUC) will be used to compare the predictability of different fitted models.

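### The school programme acts on whole schools, but the stated analysis recognises correlation only within families, so standard errors for participants aged 12 to 18 come out too small

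*Protocol article*

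**What the plan says.** The Schools section of the protocol article describes a programme aimed at whole institutions: "The program targets the whole school community including parents, students, staff, teachers and the school environment". Its age range is explicit: "All strategies are focused on adolescents aged 12 to 18 years". The enrolled schools are counted as "Twelve schools, 7 guidance and 5 high schools, across the intervention area and 15 schools (7 guidance and 8 high schools") across the control area. The components are trained principals and teachers, classroom lessons, red and green snack labels, a school health team, a smoking policy and parent meetings. Each reaches the pupils of a school together.

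The Sample size section, under Biostatistical considerations, sets the unit of analysis: "In most of analyses we will considered each individual separately, however, for interfamilial relations we will consider intraclass correlations in analyses". The sampling cluster it names is the health centre: "each health center in district 13 was a cluster and families in three randomly selected centers were recruited". For group comparisons it states "Continuous variables will be compared between intervention and control groups using student's t-test", and for proportions "Chi-square test of independence and Fisher exact test will be employed". School appears nowhere as a cluster, a random effect or a unit of analysis.

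**The concern.** The t-test and chi-square test in standard form assume independent observations. Pupils of one school share teachers, policy, food supply and peers, so their smoking, activity and weight are likely to be correlated. An adjustment for family does not absorb this, because most schoolmates are unrelated. If the text is followed as written, adolescent comparisons will have confidence intervals that are too narrow and will reach significance too often.

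This is more than detail left to a fuller plan. The article states the unit (the individual, in most analyses) and the one level at which correlation enters (family), and that choice does not match the delivery it describes. Schoolchildren are a named target group, and the discussion of intervention sites puts the emphasis on schoolchildren and adolescents.

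**Working it through.** **The plan's own figures.** No sample size or error calculation is stated for the school component. The only between-group figure is the phase 2 intervention sample of 4750, "based on 5% decrease in serum cholesterol, two gender, three age groups", with a 5% design effect and 30% attrition. It cannot be reproduced or refuted, because the cholesterol mean, SD, alpha and power for that calculation are not given.

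**Inputs from the article.** 15005 participants; 22% aged 10–19 (Table 2); 12 + 15 = 27 schools; dietary data in one tenth of participating families (Medical history and clinical examination).

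**Assumptions.** Ages 12–18 make up 7/10 of the 10–19 group; schools are of equal size; school ICC is 0.005 to 0.02.

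**Pupils per school (m).**
- All attend the 27 schools: 15005 × 0.22 × 0.7 = 2311; 2311 / 27 = 85.6. This is an upper bound, because nothing says that every cohort adolescent attends one of these schools.
- Half attend: 42.8.
- Dietary outcomes, one tenth of the full number: 8.6.

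**Formulas.** Design effect DE = 1 + (m − 1) × ICC. The true standard error is √DE times the naive one. True two-sided error of a nominal 5% test = 2 × [1 − Φ(1.96 / √DE)].

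| Case | ICC | DE | √DE | True error |
|---|---|---|---|---|
| All attend (m = 85.6) | 0.005 | 1.42 | 1.19 | 10.0% |
| | 0.01 | 1.85 | 1.36 | 14.9% |
| | 0.02 | 2.69 | 1.64 | 23.2% |
| Half attend (m = 42.8) | 0.005 | 1.21 | 1.10 | 7.5% |
| | 0.01 | 1.42 | 1.19 | 10.0% |
| | 0.02 | 1.84 | 1.36 | 14.8% |
| Dietary (m = 8.6) | 0.005 | 1.04 | 1.02 | 5.4% |
| | 0.01 | 1.08 | 1.04 | 5.9% |
| | 0.02 | 1.15 | 1.07 | 6.8% |

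**Check by group.** Intervention pupils: 5630 × 0.22 × 0.7 = 867, or 72 per school. Control pupils: 9375 × 0.22 × 0.7 = 1444, or 96 per school. With SE factor = √[(DE_i/n_i + DE_c/n_c) / (1/n_i + 1/n_c)], the factors are 1.18, 1.34 and 1.61, and the errors 9.8%, 14.4% and 22.5%. At half attendance the errors are 7.3%, 9.7% and 14.3%. The pooled figures hold.

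**Could the stated design effect already cover schools?** Read as a factor of 1.05, the phase 2 allowance implies a school ICC of 0.05 / (85.6 − 1) = 0.0006, or 0.05 / (42.8 − 1) = 0.0012 at half attendance. The article names no level for it, and it belongs to the sample size, not the analysis.

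**The case against.** The best case for the plan has three parts. First, the trial's goals concern the whole population, phase 2 was sized on cholesterol, and the school work is called a subprogram. The wording on individual analysis covers most analyses, not all, and the article says methods vary by report. This limits the weight of the point. It does not remove it, because no school-level method is stated to fill the room left.

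Second, family is not the only clustering in the document: the health centre is named as a sampling cluster, and both sample sizes carry a design effect. That is right. The accurate statement is that family is the only level named for correlation in the analysis.

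Third, the size is uncertain. Neither the ICC nor the number of cohort pupils per school is given, schools were chosen partly by distance, and dietary data are sparse. This stands, and it is why the result is a range with an upper bound.

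Two stronger readings are tempting, and the documents support neither.
- A reader might apply the calculation to the knowledge, attitude and practice survey of 7669 adolescents and obtain far larger errors. That survey served to design the education programme and is repeated to guide further teaching. No group test on it is stated, and nothing places its respondents in the 27 schools. It also exceeds the whole cohort aged 10–19 (15005 × 0.22 = 3301).
- A reader might take 12 against 15 schools as genuine replication of the intervention. Schools were not allocated independently. One health-centre area received the intervention and two served as controls, and schools were chosen within those areas. All 12 intervention schools therefore share one area.

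**Conclusion.** The concern holds for between-group comparisons in participants aged 12 to 18. The direction is certain for any positive school ICC; the amount rests on the assumed ICC, the assumed age share and attendance at the 27 schools. On those assumptions the true error of a nominal 5% test is about 10 to 23% at most, about 7 to 15% if half the pupils attend these schools, and about 5 to 7% for dietary outcomes, where the effect is slight. Adult outcomes are outside this point. Accounting for schools would not make the adolescent comparison equivalent to a school-randomised one, because area and treatment remain inseparable. It is worth correcting, but it is secondary to that allocation problem.

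**What to change.** In the analysis text, for between-group comparisons of outcomes at ages 12 to 18:

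- Record the school attended at each three-yearly examination, since pupils move from guidance to high school or leave, and state which examination's school applies to each outcome.
- Account for school in addition to family, by a random effect or by school-level summaries, with guidance or high school as a factor and small-sample degrees of freedom based on the number of schools.
- Keep pupils in the group of their residence. The article puts the crossover of students between areas at under 8%.
- Report the school ICC.
- State that this corrects school-level correlation only, that area stays confounded with treatment, and that the 12 and 15 schools are not replicates of the allocation.

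The cost is one extra recorded field, some analysis wording, and wider confidence intervals for adolescent outcomes. Recruitment and the intervention do not change.

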#### Classroom curriculum and practice

The classroom curricula based on life skills training to prevent tobacco use in adolescents were designed to increase the knowledge, modify the attitude and especially skills of students for living tobacco free. Nine 45-min lessons were delivered by trained teachers during the first year of intervention for all grades in high schools. The school sessions were followed by activities of teachers, parents, and in particular a core called "health team" which is compose of one volunteer representative from each class in each school headed by one of the trained teachers. The team has an advisory role of anti smoking policies, nutrition guidance and physical activity in the school.

Proclaiming the importance of physical activity, morning exercises, theoretical and practical trainings for schoolchildren, encouraging the children to be a member of a sport team in school and arranging some sport competitions are among intervention components in the schools.

#### Peer teaching

On the base of peer-teaching approach, this component aims at establishing a school health team consisted of representative students is formed and headed by one of the trained teachers. The team has an advisory role for anti-smoking policies, nutrition guidance and physical activity programs in each school and creating supportive leadership for students' activities in the society by the principal and other staff. Each class has a representative in the school health society and all of the members work together to promote healthful lifestyle in the schoolchildren and to extend positive health behaviors. In each class, a health team consisted of representative students is formed and headed by one of the trained teachers. The team has an advisory role for anti-smoking policies, nutrition guidance and physical activity programs in the school.

#### Anti-smoking policy in schools

Includes smoking prohibition for all the schoolchildren, teachers and employees, smoking abandonment for smokers and supporting the smoking prohibition program are among anti-smoking policy.

Educational posters and pamphlets and lectures related to various aspects of lifestyle modification are given during parents meetings.

#### Family (parents) involvement

The aim of the family involvement component is to introduce families to the school-based lifestyle modification subprogram and assist them in creating a supportive environment for living tobacco-free and healthy behaviors. This component includes a series of interactive forum to discuss the extent of NCD risk factors among schoolchildren and families and also practical aspects of the program during ordinary meetings of the parent-teachers society in each school.

### Families

Training instructions are specially developed according to the baseline data and KAP studies. Pamphlets, face to face interviews, concomitant meetings and training sessions are provided for lifestyle modification. Stress control educational sessions, advisory stress clinics, and some written brochures and booklets related to coping with stress are among other family based activities.

Regarding physical activity, subjects are categorized into 5 groups: those who are physically inactive, those with enough motivation but not good physical activity level, those who have irregular physical activity, those who have regular physical activity less than 6 months and those with regular physical activity more than 6 months. Special programs are developed for each group of physical activity.

### Concomitant conditions

Medical illnesses requiring treatment that could affect implementation of TLGS study protocol are not considered to be important intervening factors. Participants having conditions or illnesses related to risk factor are advised to attend TLGS clinics or visit their own private physicians. All concomitant medical conditions are recorded in yearly telephone calls and outcomes are completely sought. Use of medications, applications of procedures and occurrence of any disease are registered in every 3 year fact-to-face visits.

### Retention

For a large prospective study such as the TLGS, the retention of a large proportion of the study participants throughout the follow up is key issue to the statistical power and validity of the findings. In the first phase of the study, several potential obstacles to retention were identified, such as dissatisfaction with allocated time, masking of some of the results, transportation of elderly, child and elder care, and lack of medical care, which varied considerably among the study families. Steps to maximize retention were based on recognizing these barriers and committing efforts and resources for their removal.

Comprehensive educational procedures with responsive continuously available professional staff, motivation programs, group activities, rewards and quarterly health newsletter to encourage sense of community within the TLGS, were among many activities to help to minimize dropouts. Program coordinators and social workers were trained in skillful interviewing based on reflective listening, expression of empathy and acceptance of ambivalence, in order to approach behavior change in participants [47].

A computer-based monitoring system [48] allows identification of participants not attending visits and mechanisms are in place to recover those who no longer actively participate. Questionnaires are administered to determine the negative and positive impact of the study. Social workers continue to contact inactive participants to remind them of the opportunity to have a new appointment for delivering new data for each period of the study.

### Approval

This study has been approved by the National Research Council of the Islamic Republic of Iran (No. 121) and has been performed with the approval of the Human Research Review Committee of the Endocrine Research Center, Shahid Beheshti University (M. C).

### Biostatistical considerations

#### Sample size

For baseline data collection, based on predicted prevalence rates of 30% for dyslipidemia in people <30 and 45% for those ≥ 30 years of age, confidence interval of 95%, study power of 80%, attrition rate of 20%, design effect of 2% for seven age groups and two sexes, sample size was calculated to be 14280. Therefore, 15005 subjects were selected randomly from areas covered by 3 health centers. In phase 2 of TLGS, based on 5% decrease in serum cholesterol, two gender, three age groups, 5% design effect and 30% attrition rate, sample size for intervention group was calculated as 4750 subjects. Therefore, population covered by one of the 3 health centers (5630 people) selected for intervention and 9375 subjects under coverage of other two centers used as controls.

Because of the wide scope of the project and variety of the measured variables, different types of analyses are performed, depending on the type of the reports or the variables and outcomes.

Although the original of this study was based on reducing hypercholesterolemia, however, in all subjects including those less healthy or normals, changes in other risk factors, NCD, and outcomes delineated in this study will also be followed in statistical considerations.

In most of analyses we will considered each individual separately, however, for interfamilial relations we will consider intraclass correlations in analyses. It should be also mentioned that in multistage cluster random sampling procedure, each health center in district 13 was a cluster and families in three randomly selected centers were recruited. Continuous data are expressed as their measures of location and spread in total and subgroups. For qualitative and categorized continuous variables, percentages and frequency distributions are reported.

Normality of distribution of the continuous variables will be examined using histograms, measures of skewness and kurtosis, Kolmogrove-Smirnove test and sometimes Chi-square test. When log-transformed values are used, geometric means are computed. Percentiles will be used to describe the high or low values of the skewed variables. When assumptions of the parametric statistical methods are not met, nonparametric methods of their counterparts will be used. These methods also were used for analysis of variables, not originally continuous, such as attitudes, quality of life etc.

Incidence rates of NCDs such as diabetes mellitus, angina pectoris, myocardial infarction, hypertension etc., will be estimated adjusted mainly for age and sex. Relative risks for different factors and their 95% confidence interval will be reported.

Continuous variables will be compared between intervention and control groups using student's t-test. Analysis of variance (ANOVA) will be used to compare the variables among three or more subgroups followed by appropriate post hoc test such as Tukey. To adjust the comparison by the potential confounding variables, two or three-way ANOVA will be used. In addition, analysis of covariance will be employed when adjusting for a covariate correlated with the dependent variable. To compare the proportions between two or more groups, Chi-square test of independence and Fisher exact test will be employed. Matel-Haenszel test will be used when adjustment required. To compare the data with their baseline, paired t-test and repeated measures analysis of variance or McNemar, Sign and Friedman tests will be used.

To evaluate the relationship between variables, Pearson or Spearman correlation coefficients is used Multiple regression analysis will be used to find out the relationship between variables such as blood pressure, fasting blood sugar, lipid profiles and variables regarded as independent variables such as body mass index, waist circumference, lipid profiles, age, etc.

When the outcome variable was defined as dichotomous, for instance, diabetes mellitus, hypertension, etc., multiple logistic regressions was employed to assess the relation of potential risk factors and the outcomes. Multinomial logistic regression will be used when the outcome is defined as polychromous variable, e.g., diabetes mellitus, impaired glucose tolerance (IGT) and normal. Odds ratio and its confidence interval will be reported and interpreted. Secondary outcomes (e.g., mortality, cardiovascular morbidity) will be analyzed using life table method to evaluate the association of different factors on survival time, Cox regression analysis was performed. A proportional hazards regression model will be used to evaluate potential covariability that may modify the primary and secondary outcomes. The adequacy of the models will be checked, usually, using the Hosmer-Lemeshaw statistic. In addition, ROC curve and its area under curve (AUC) will be used to compare the predictability of different fitted models.

In some applications, in order to summarize the data and reduce its dimension, factor analysis using principal component method and varimax rotation will be performed.

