#### Study population

A total of 15005 individuals aged 3 years and over who were residence of district No.13 of Tehran and were under the coverage of three medical health centers, were selected using multistage cluster random sampling method. All members of each family, including those not having risk factors, were invited for baseline measurements and will be followed every 3 years. A map of areas of intervention and control groups in district 13 is presented in figure 1. District No. 13, one of the 22 districts of Tehran metropolitan city which it is located in the eastern part of the city and covers the area of about 13 sq. kms and is under coverage of Shahid Beheshti University of Medical Sciences and Health Services was selected. Then three medical health centers of overall 20 medical health centers in the district were selected. As a commentary, all medical health centers in this district have the filed data of almost all covered families (over 90%) and enjoy a well-developed framework of experienced health volunteers (Rabet-e Behdasht) who play a crucial role in the recruitment of people in the study and distribution of written educational documents. They help the study personnel to improve the knowledge and attitude of the study population in the intervention area. A complete demographic database of all families in three centers including family dimension, gender, age, and postal address and telephone numbers were extracted from data in medical centers. Based on the given data, every family was contacted, invited, and then recruited to participate in the study. Age distribution and socioeconomic status of the population in district No. 13 is representative of overall population of Tehran (Iran National Census, 1996) [9]. (Table 2)

**Table 2 T2:** Age distribution in study population, Tehran, and Iran urban inhabitants.

Age group (year)	Study population (%)	Tehran urban inhabitants (%)	Iran urban inhabitants (%)
0–9	15	18	22
10–19	22	25	27
20–29	18	19	17
30–39	16	16	14
40–49	11	11	9
50–59	9	6	5
60–69	9	5	6

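### The 4750 behind the single intervention centre allows a design effect of only 5%, which leaves almost no room for variation between health centres, although the centre is the stated cluster

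*Protocol article*

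**What the plan says.** All of this is in the protocol article. Under Sample size (Biostatistical considerations), the phase 2 calculation is described as "based on 5% decrease in serum cholesterol, two gender, three age groups, 5% design effect and 30% attrition rate", which gives 4750 for the intervention group. The text then concludes that the population of one centre (5630) is taken for intervention and that the other two centres (9375) serve as controls.

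The baseline survey is treated in the same style: "attrition rate of 20%, design effect of 2% for seven age groups and two sexes, sample size was calculated to be 14280".

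The same section says that each health centre in the district was a cluster and that families were recruited within three centres. Study population adds the family level: "All members of each family, including those not having risk factors, were invited for baseline measurements". Most analyses are to treat individuals separately, with intraclass correlation considered only for family relations. Continuous variables are to be compared between the groups by Student's t-test. No ICC is given for centre or family.

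**The concern.** A design effect is the ratio of the variance under the actual design to the variance under simple random sampling. It grows with cluster size: even a very small correlation between people of one centre matters when the cluster holds thousands. An allowance of 5% looks like a figure for very small clusters, not for an arm made of a single centre.

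The article draws its choice of one centre from 4750. If the clustering allowance does not fit the design, any precision or power read from 4750 or 5630 is too favourable. The planned individual-level t-test would not correct this, because it takes no account of centre.

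**Working it through.** **Inputs from the article (Sample size):** design effect 5%, read as 1.05; attrition 30%; six sex-by-age cells; 4750 calculated; 5630 taken; one intervention centre.
**Assumed:** centre ICCs of 0.001 and 0.005, because the article gives none.

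**1. Can 4750 be rebuilt?** No. Mean cholesterol, its standard deviation, alpha and power are not stated for phase 2. One can only work backwards:
- attrition as division by 0.70: 4750/6 × 0.70/1.05 = 528 per cell
- attrition as multiplication by 1.30: 4750/(6 × 1.05 × 1.30) = 580 per cell

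Neither confirms the total, since any design effect can be solved for in this way. The baseline 14280 is just as uninformative: 14 × 800 × 1.02/0.80 and 14 × 425 × 2 × 1.2 both equal 14280.

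**2. People retained in the intervention centre.** 5630 × 0.70 = 3941. At 1.05 they count as 3941/1.05 = 3753 independent people.

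**3. Centre ICC that 1.05 requires.** DE = 1 + (m − 1) × ICC, so ICC = (DE − 1)/(m − 1).
- Whole centre: 0.05/3940 = 0.0000127
- One sex-age cell (3941/6 = 657): 0.05/656 = 0.000076
- If 5% was a misprint for a design effect of 5: 4/3940 = 0.0010

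**4. Effective size.** n_eff = 3941/(1 + 3940 × ICC). The last column is the standard error of the centre mean relative to the one implied by 1.05, √(DE/1.05).

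| Centre ICC | DE | Effective n | Relative standard error |
|---|---|---|---|
| as planned | 1.05 | 3753 | 1.0 |
| 0.001 (assumed) | 4.94 | 798 | 2.2 |
| 0.005 (assumed) | 20.7 | 190 | 4.4 |

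Within one cell of 657 the loss is smaller but still material: 657/1.05 = 626 as planned, 657/1.656 = 397 at ICC 0.001, and 657/4.28 = about 154 at 0.005.

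**5. Does the surplus over 4750 help?** For any ICC below 1, n_eff is less than 1/ICC, here 1000 or 200. With 4750 enrolled, 3325 are retained, and n_eff is 3325/4.324 = 769 at ICC 0.001 and 3325/17.62 = 189 at 0.005. The 616 additional completers from 5630 (3941 − 3325) add about 29 effective people in the first case and one or two in the second.

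**The case against.** The strongest defence is that no ICC is given, so every loss above rests on an assumed value, and that 4750 cannot be shown to be miscalculated. Both statements are true. A reader might infer that the totals contain an arithmetic slip, or that 1.05 is impossible. The article supports neither: too many inputs are unstated, and 1.05 is possible at a centre ICC near 0.00001. What stands is that the article names the centre as the cluster and uses an allowance with almost no room for it.

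The percentages may be misprints. That does not remove the point, because even a design effect of 5 needs a centre ICC of about 0.001 or less.

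5630 exceeds 4750, which leaves room for a design effect of 5630/4750 × 1.05 = 1.24 at the same effective size. This too covers a centre ICC of only 0.2445/3940 = 0.00006.

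A reader might also infer that family clustering alone makes the pooled comparison too small. It does not follow. Since 4750 was built from six cells, a pooled comparison for the same effect needs only about one cell's number. With five members per family and a family ICC of 0.3 (both assumed), DE = 1 + 4 × 0.3 = 2.2, and 528 × 2.2/0.70 = about 1660 enrolled, well below 5630. Nor is the pooled comparison shown to be short at every centre ICC: 798 still exceeds the back-solved 528, whereas 190 does not.

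Finally, the remark "Although the original of this study was based on reducing hypercholesterolemia" might suggest that the target was a prevalence. The sample-size sentence itself states a decrease in serum cholesterol, a concentration, so sizes or power for a prevalence target would test something it does not state.

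**Conclusion.** The concern holds for the clustering allowance. The 4750 that justifies one intervention centre implies a precision that the design supports only if centre-level variation is practically nil (centre ICC about 0.00001 or less, with 3941 retained). The direction of the error is clear. Its size rests on assumption: at centre ICCs of 0.001 and 0.005 the effective size is about 798 and 190 in place of 3753. The calculation takes 1.05 literally and assumes that 30% are lost from 5630.

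No larger design effect would cure the underlying limit. With a single centre under intervention, whatever distinguishes that centre from the other two cannot be separated from the effect of the programme. That limits inference and should be stated as such. It is not a reason to call 4750 an arithmetic error.

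**What to change.** Keep enrolment as it is and rewrite the sample-size paragraph so that it:

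- describes the design effect as a variance ratio, and corrects the 2% and 5% if they are misprints;
- says that 1.05 covers at most family clustering within sex-age cells, and that 4750 assumes no centre-level variation;
- gives the effective sample size and the detectable difference in mean cholesterol over a stated range of centre ICC, for example 0 to 0.005, with the mean, standard deviation, alpha and power used;
- states, as a limit on inference, that with one intervention centre the variation between centres cannot be separated from the intervention effect.

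The cost is one rewritten paragraph and a less favourable statement of precision. No participants are added.
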